## Abstract

**Background:**

Smallholder farmers receive educational interventions on safe pesticide handling by governmental agencies, industries, or nongovernmental organizations to reduce exposure risks. However, existing educational interventions have limited effects on changing behaviors. Targeting psychosocial determinants of behavior change in educational interventions through theory- and evidence-based approaches may enhance their effectiveness.

**Objective:**

We aim at describing the intervention development and study design of a 3-arm cluster-randomized controlled trial to assess the effects in improving safe pesticide handling and reducing pesticide exposure of (1) an existing educational intervention and (2) a newly developed SMS text messaging intervention based on the Risks, Attitudes, Norms, Abilities, and Self-regulation (RANAS) behavior change approach.

**Methods:**

We enrolled 539 Ugandan smallholder farmers in 12 clusters (subcounties). The clusters, each with 45 farmers, were randomly allocated to one of the three arms: (1) educational intervention, (2) educational intervention+RANAS-based SMS text messages, or (3) control group. The educational intervention comprised a 2-day workshop that targeted multiple aspects of safe pesticide handling, whereas the SMS text messages targeted the use of personal protective equipment (PPE) and were based on the RANAS approach. For intervention development in this study, this approach includes identifying psychosocial determinants of PPE use at baseline and selecting behavior change techniques to target them in SMS text messages. The primary outcomes of the study are (1) pesticide knowledge, attitude, and practice scores indicating performance throughout the educational intervention; and (2) frequency of PPE use. Secondary outcomes are the RANAS-based behavioral determinants of PPE use, the frequency of glove use, algorithm-based pesticide exposure intensity scores, and signs and symptoms of pesticide poisoning. The outcomes were assessed in structured interviews before the intervention (baseline) and at the 12-month follow-up. The effect of the interventions among the arms will be analyzed using the intervention arms and baseline measures as predictors and the follow-up measures as outcomes in linear multivariable mixed models including the clusters as random effects. The mediating psychosocial determinants of the interventions will be assessed in multiple mediation models.

**Results:**

The study was conducted from 2020 to 2021—baseline interviews were conducted in October 2020, and the educational intervention was delivered in November 2020. The RANAS-based SMS text messages were developed based on the baseline data for relevant behavioral determinants of PPE use and sent between February 2021 and September 2021. Follow-up interviews were conducted in October 2021. Overall, 539 farmers were enrolled in the study at baseline; 8.3% (45/539) were lost to follow-up by the end of the study.

**Conclusions:**

This study will contribute to a better understanding of the effectiveness and behavior change mechanisms of educational interventions by using an experimental, cluster-randomized study design to improve pesticide handling among smallholder farmers.

**Trial Registration:**

International Standard Randomised Controlled Trial Number (ISRCTN) 18237656; https://doi.org/10.1186/ISRCTN18237656

**International Registered Report Identifier (IRRID):**

DERR1-10.2196/55238

## Introduction

### Background

Agricultural pesticide use has almost doubled worldwide in the past 3 decades, with a particular increase in low- and middle-income countries (LMICs) [1]. For example, in Uganda, there was a 12-fold increase in pesticide import value between 2000 (US $9.4 million) and 2020 (US $108.5 million) [2]. The increase in pesticide use results from many factors, such as the intensification of agricultural systems, changing land use patterns due to climate change [3], pesticide resistance, or increasing pest pressure [4]. In most LMICs, smallholder farmers dominate agricultural production [5], mainly relying on pesticides as their primary and often their only pest control strategy [6,7]. However, smallholder farmers often have insufficient knowledge, attitude, and practice (KAP) along the pesticide-handling chain, for example, limited knowledge of hazard information present on pesticide labels [8], low risk perception of the product [6,9], and limited use of recommended personal protective equipment (PPE) [6]. Hence, these gaps in the KAP of pesticide handling may risk farmers’ health [10,11].

The agricultural extension service system that ought to provide technical advice to improve farmers’ skills in pest control [12] and on safe pesticide handling [13] is often constrained by low staffing in LMICs. Therefore, it does not effectively reach out to farmers [4]. Consequently, smallholder farmers obtain most of their pesticide use information from their counterparts and agro-dealers [6]. However, agro-dealers often lack sufficient legal and technical qualifications to guide farmers on safe pesticide handling in LMICs [10,14]. Alongside these information channels, interventions promoting safe pesticide handling by smallholder farmers are rolled out by governmental agencies, industries, or nongovernmental organizations (NGOs) worldwide [15]. These interventions can be classified as educational or behavioral [16], technological or engineering-based, legislation- or enforcement-focused, incentive-based, and multifaceted interventions [15]. They range from creating awareness to promoting the use of PPE, adherence to manufacturers’ instructions, use of low-toxicity–class pesticides and other pest control strategies, and policy advocacy. By 2022, a total of 3 intervention studies had been systematically assessed for their impacts in reducing pesticide exposure in Africa [17]. Of these studies, 2 provided insight into the importance of farmer field schools in promoting integrated pest management (IPM) and, consequently, reducing pesticide use among smallholder farmers [18,19]. The other study provided evidence that training health care workers improves their knowledge and skill in handling acute pesticide poisoning cases [20].

In Uganda, educational interventions on pest management and safe pesticide use are mainly conducted by NGOs or industries [21]. These educational interventions, for example, reduced pesticide application frequency, increased PPE use, and introduced IPM strategies [18]. Similar findings are reported in other LMICs. For example, in Bolivia, trained farmers that adhered to safe pesticide use practices had considerably lower urinary pesticide metabolite levels after pesticide application than the untrained farmers [22]. Similarly, in Costa Rica, lower self-reported pesticide exposure intensity scores (EISs) among farmers were observed in farmers who had attended training in safe pesticide handling [23]. In summary, the existing literature on pesticide intervention evaluations in LMICs is limited by (1) cross-sectional study designs; (2) no comparative assessment of the impact on KAP; and (3) no systematic approach to targeting and assessing behavioral determinants of pesticide handling, such as farmers’ psychosocial cognitions [24].

One way to systematically change behavior is the Risks, Attitudes, Norms, Abilities, and Self-regulation (RANAS) framework [25]. The RANAS approach is an established tool that suggests different steps for designing and evaluating evidence- and theory-based behavior change interventions based on proposed psychosocial behavioral determinants [26]. This study protocol showcases the study design of a randomized
controlled trial to evaluate and an enhance existing educational interventions using the RANAS approach for systematic behavior change [25] to promote safe pesticide handling among smallholder farmers in Uganda. This study is part of the African Pesticide Intervention Project, which seeks to promote and improve intervention studies on pesticide handling in LMICs [27].

### Aims and Specific Objectives of the Study

There are two main aims to this study (Figure 1): o evaluate the effectiveness of an existing educational intervention on pesticide-related KAP, PPE use, exposure, and health risks of pesticide handling; and (2) to evaluate whether the effect of the educational intervention can be enhanced by sending tailored RANAS-based SMS text messages targeting behavioral determinants of PPE use among smallholder farmers in Uganda. In relation to the first aim, the following outcomes are addressed:

To investigate the effect of the educational intervention on pesticide-related KAP along the educational curriculum compared to the control.To assess the effect of the educational intervention on pesticide exposure intensity compared to controls.To assess the effect of the educational intervention on health signs and symptoms associated with acute pesticide poisoning compared to controls.

In relation to aim 2, the specific research questions are as follows:

To test whether SMS text messages that targeted behavioral determinants based on the RANAS approach for behavior change have an additional, increased effect on PPE use compared to the educational intervention alone.To understand which behavioral determinants specified by the RANAS approach were enhanced by the intervention and explain behavior change regarding PPE use.

**Figure 1 figure1:**
[figure not shown]
Conceptual framework showcasing the 5 objectives and their outcome measures to evaluate the existing educational intervention (2-day workshop) and the newly designed Risks, Attitudes, Norms, Abilities, and Self-regulation (RANAS)–based SMS text messaging intervention on safe pesticide handling among smallholder farmers in Uganda. PPE: personal protective equipment.

## Methods

### Study Design

A cluster-randomized controlled trial with 3 arms—educational intervention, educational intervention and RANAS-based SMS text messages, and a control arm (received no intervention; Figure 2)—was conducted in the Kumi and Sembabule districts of Uganda between October 2020 and October 2021. A video describing the study can be found in Multimedia Appendix 1. A total of 12 subcounties (6 from either district), which are geographical administrative units of lower local government, formed the clusters for the study.

**Figure 2 figure2:**
[figure not shown]
(A) Study design of the 3-arm cluster-randomized controlled trial to evaluate the educational intervention (2-day workshop) and the newly designed Risks, Attitudes, Norms, Abilities, and Self-regulation (RANAS)–based SMS text messaging intervention on safe pesticide handling. (B) Timeline of the 3-arm cluster-randomized controlled trial.

### Study Area

Sembabule District is located in the central region of Uganda and has 6 subcounties and 2 town councils. Kumi District, on the other hand, is situated in the eastern region and subdivided into 6 subcounties and 1 municipality (Figure 3). The 6 subcounties from each district were selected based on their rural setting associated with ongoing agricultural activities. Both districts have pesticide-intensive crop (eg, watermelon, tomato, cabbage, and passion fruit) and livestock (eg, cattle, goats, and sheep) production systems, which constitute major economic activities.

**Figure 3 figure3:**
[figure not shown]
A map of Uganda showing the 2 study districts and intervention allocation of the subcounties. RANAS: Risks, Attitudes, Norms, Abilities, and Self-regulation.

### Participants

The District Farmers’ Associations (DFAs)—the Sembabule DFA and the Kumi DFA—provided lists of farmers who (1) grew at least one of the crops (watermelon, tomato, cabbage, and passion fruit) that are locally associated with frequent pesticide use, (2) had been actively involved in pesticide application in the previous 12 months, (3) were aged ≥18 years, (4) were able to read and write in English or the local language, (5) belonged to a household with at least one active mobile phone, and (6) had not directly participated in previous Uganda National Association of Community and Occupational Health (UNACOH)–led trainings in the area. Each of the DFAs provided a list each comprising 300 smallholder farmer names and contacts from their database, providing a total of 600 eligible participants, 50 from each subcounty. The research assistants contacted the farmers and interviewed (at baseline and 12 months afterward) those available and obtained consent until 45 farmers per subcounty were enrolled. The interviews took place at the farmers’ homes or fields depending on the farmers’ location at that time.

### Ethical Considerations

Ethics approval for the study was secured from the Higher Degrees, Research, and Ethics Committee at Makerere University in Uganda (reference 846). In addition, the study was registered on the ISRCTN clinical trial registry (ISRCTN 18237656), and written informed consent was obtained from all study participants before the baseline interview.

### Randomization and Blinding

After the baseline survey in October 2020, a total of 4 clusters each with 45 farmers were randomly assigned to one of the three arms, comprising 180 farmers per arm (Figure 1): (1) educational intervention, (2) educational intervention+RANAS-based SMS text messages, or (3) control group. One of the Swiss investigators who had no previous knowledge of the subcounties used Microsoft Excel (Microsoft Corp) random numbers to randomize the clusters to the arms. The allocation of the clusters was concealed from the participants. The participants were also blinded with regard to which arm other farmers had been assigned to. The investigators and facilitators knew which arm the farmers had been assigned to, and at the follow-up interviews, the research assistants could know which arm the farmers had been assigned to.

### Sample Size Calculation

We estimated a sample size of 540 farmers that assumed a statistical power of 80% based on the estimated observed differences between the EISs of an average pesticide application between smallholder farmers who received training in pesticide handling and those who did not receive it in a recent survey in Uganda [23]. The trained group had a mean EIS of 0.47 (SD 0.10), and the untrained group had a mean EIS of 0.55 (SD 0.18). We assumed that the 2 planned intervention arms would show a similar effect distribution. Hence, we based our sample size calculation on the 2-sample means test assuming a cluster-randomized design, a total of 12 clusters equally distributed between the control and intervention groups, and an intraclass correlation coefficient of 0.4. The package *power two means* in the statistical software Stata (version 15; StataCorp) resulted in a cluster size of 40 farmers and a total of 480 farmers, which would reach a power of 80% at a significance level of 5%. To account for a possible dropout rate of 13% at follow-up based on a previous study in a similar setting [23], in each cluster, an additional 5 farmers were enrolled, hence constituting a total sample size of 540.

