##### Step 2 of RANAS-Based Intervention Development: Identifying Behavioral Determinants of PPE-Related Intentions and Behaviors at Baseline

Different contexts, behaviors, and persons may presuppose the expression of different psychosocial behavioral determinants, which need to be identified in a baseline assessment (step 2). To identify the determinants that are relevant when promoting PPE use among Ugandan smallholder farmers, we assessed all psychosocial determinants described by the RANAS approach at baseline (see the Outcome Measures section; ie, psychosocial determinants related to pursuing PPE use and using PPE). Multiple regression analyses were then computed to identify which determinants were related to higher behavior and intention to pursue PPE use and use PPE. In total, 4 regression models were calculated using the following dependent variables: intention to buy PPE, intention to use PPE, number of PPE items owned, and frequency of PPE use.

The baseline analyses of all 3 study groups before the interventions revealed that farmers owned PPE to cover an average of 4 (out of 8; SD 1.6) body parts. The accumulated frequency of using PPE to cover all body parts was 4.1 (SD 2.8), with a possible range of 0 (never covering any body part) to 40 (always covering all body parts). This mean corresponds to 10% (SD 7%) of full body, consistent use (always covering all body parts with PPE=100%). The regression analyses (Table 1) indicated the following:

Farmers’ intention to buy PPE was higher when they considered themselves more vulnerable to health risks, perceived the health risks of pesticides to be less severe, perceived wearing PPE as more time consuming, felt proud of using PPE, perceived other people to approve of PPE use more, and had an action plan for where to buy PPE, as well as when they were more committed to using PPE.Farmers’ intention to buy PPE was higher when they perceived higher response efficacy and were more committed to using PPE.Farmers owned more PPE items when they perceived the costs to be lower, perceived other farmers to use PPE, had an action plan for where to buy PPE, and had a coping plan in the sense of overcoming arising barriers to using PEE and pursuing more PPE.Farmers used PPE more frequently when they perceived the costs to be lower, perceived other farmers to use PPE, had an action plan for where to buy PPE, and had a coping plan in the sense of overcoming arising barriers to using PPE pursued more PPE.

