### Outcome Measures

#### Overview

The coprimary outcomes of the study are (1) pesticide KAP scores indicating performance along the educational curriculum and (2) PPE use (to cover all body parts). Secondary outcomes are the psychosocial determinants based on the RANAS framework regarding PPE use, frequency of using gloves when handling pesticides, algorithm-based pesticide EISs, and frequency of health signs and symptoms associated with pesticide poisoning. All measures were self-reported. The full questionnaire, programmed to be used in Open Data Kit (ODK; Get ODK Inc), can be found in Multimedia Appendix 5. Items using Likert scales had 5 answer options and were augmented with a visual 5-dot scale to increase participants’ understanding, as has been shown to be helpful in other studies to support responding populations with low literacy [26]. The outcomes are summarized in Textbox 1.

Summary of the objectives and outcomes of the study.

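### The sample size rests on an effect for EIS, a secondary outcome, so the stated 80% power covers neither coprimary outcome, and its own inputs do not give 80% even for EIS

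*Protocol article*

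**What the plan says.** The Sample Size Calculation section bases the 540 farmers on EIS, "based on the estimated observed differences between the EISs of an average pesticide application between smallholder farmers who received training in pesticide handling" and farmers who did not. Its effect-size inputs are: "The trained group had a mean EIS of 0.47 (SD 0.10), and the untrained group had a mean EIS of 0.55 (SD 0.18"). The other inputs are "a total of 12 clusters equally distributed between the control and intervention groups, and an intraclass correlation coefficient of 0.4", a 5% significance level and 80% power. The Stata routine "resulted in a cluster size of 40 farmers and a total of 480 farmers", and five farmers per cluster were added for 13% dropout. The section also assumes that the two intervention arms would show similar effects.

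Outcome Measures (Overview) states: "The coprimary outcomes of the study are (1) pesticide KAP scores indicating performance along the educational curriculum and (2) PPE use (to cover all body". The same paragraph and the Abstract place EIS among the secondary outcomes.

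Randomization and Blinding gives four clusters of 45 to each of three arms, so every pairwise contrast is 4 versus 4 clusters. Aim 2 asks whether the SMS messages add to the educational intervention's effect on PPE use.

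**The concern.** A power statement holds only for the outcome, difference and contrast it was computed for. Here that is EIS, trained versus untrained, with the clusters split into two equal groups. The coprimary outcomes are a 0-16 knowledge score, 5-point attitude and practice scores, and a PPE-use frequency summed over body parts. A difference of 0.08 in EIS implies no particular difference on any of these. The section gives no target difference, SD or ICC for them.

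The SMS contrast is further from the calculation still. Treating the two intervention arms as alike gives no difference between them to detect.

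The 80% is the only power figure in the article. A non-significant coprimary result could be read against it as evidence of no effect from an adequately powered trial.

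**Working it through.** **Inputs from the documents.** Means 0.47 and 0.55, SDs 0.10 and 0.18, 12 clusters in two equal groups, 40 per cluster, ICC 0.4, alpha 5%, power 80% (Sample Size Calculation). Four clusters per arm (Randomization and Blinding). Sidedness is not stated; two-sided is assumed.

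**Step 1: the plan's own figure.**
- Difference: 0.55 − 0.47 = 0.08.
- Root-mean-square SD: √[(0.10² + 0.18²)/2] = √0.0212 = 0.1456, so the standardised difference is 0.08/0.1456 = 0.55 SD.
- Design effect: 1 + (40 − 1) × 0.4 = 16.6.
- SE with 6 × 40 = 240 per group: √[16.6 × (0.0100 + 0.0324)/240] = 0.0542.
- Power: Φ(0.08/0.0542 − 1.96) = Φ(−0.48) ≈ 31%.

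The stated 80% is not reproduced. Other readings also fall short:

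| Variant (40 per cluster, ICC 0.4) | Power |
|---|---|
| 6 vs 6, t with cluster df | 27% |
| 6 vs 6, one-sided | 43% |
| 6 vs 6, common SD 0.10 | 58% |
| 6 vs 6, common SD 0.18 | 22% |
| 12 clusters in each group | 55% |

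Enlarging the clusters does not help. With unlimited cluster size the SE tends to √(0.0424 × 0.4/6) = 0.0532, and power to Φ(1.50 − 1.96) ≈ 32%. At 6 versus 6 clusters of 40, 80% would need an ICC of about 0.093.

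**Step 2: the contrasts as randomised, 4 versus 4.** With 4 × 40 = 160 per arm, SE = √(16.6 × 0.0424/160) = 0.0663. Power = Φ(0.08/0.0663 − 1.96) = Φ(−0.75) ≈ 23% (17% with cluster df).

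**Step 3: what can be said about the coprimary outcomes.** Their power cannot be computed, because no target difference or ICC is given. The detectable effect in SD units needs only an ICC:

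MDE = (1.960 + 0.842) × √{2 × [1 + 39 × ICC]/160}

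| ICC | Normal | t, 9 df (12 clusters − 3 arms) | t, 6 df (8 clusters − 2 arms) |
|---|---|---|---|
| 0.4 (plan) | 1.28 SD | 1.435 SD | 1.53 SD |
| 0.1 (assumed) | 0.69 SD | 0.779 SD | 0.83 SD |
| 0.05 (assumed) | 0.54 SD | 0.605 SD | 0.64 SD |

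Forty analysed per cluster is close to what was achieved: 494 followed up over 12 clusters is 41.2.

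**Step 4: why not in PPE-score points.** The Step 2 section of RANAS development reports: "The accumulated frequency of using PPE to cover all body parts was 4.1 (SD 2.8"), on a stated range of 0 to 40. The section on frequency of PPE use sums eight means, each coded 1 to 5, so its lowest possible score is 8 × 1 = 8. A mean of 4.1 cannot arise from that scoring. The scale of the 2.8 is therefore not established.

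**The case against.** Several points on the other side stand.

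- EIS is not the only input. ICC, number of clusters, alpha, power and dropout are stated too. EIS supplies only the effect-size inputs.
- A trial may be sized on a secondary outcome. The section says openly that it used EIS and never claims the 80% for KAP or PPE use.
- EIS is related to PPE use. In its formula the PPE factor spans 0.14 to 1, about 7-fold (1/0.14), while changing and showering each span 0.7 to 1, about 1.4-fold. Still, that factor accounts for material and body-part exposure risk, whereas the coprimary score sums frequencies. Nothing links EIS to KAP.
- The Abstract lists baseline measures as predictors. An assumed baseline/follow-up correlation of 0.5, applied to both variance components, would shrink the detectable effect by 1 − √(1 − 0.25) ≈ 13%. The table above is conservative to that extent.

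A reader might also infer more than the documents support:

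- That choosing EIS caused the low power. It did not: the 23% comes from ICC 0.4 and four clusters per arm, and any outcome with a 0.55 SD effect would give the same.
- That the trial is shown to be underpowered for KAP or PPE use. At an ICC near 0.05, a 0.55 SD effect would have about 82% power (normal approximation; 72% with 9 df), and the true ICCs are not given.
- That the calculation should have used the PPE-use SD of 2.8. That figure comes from the baseline survey of the farmers whose number the calculation set.

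**Conclusion.** The concern holds in this form. EIS supplies the only effect-size inputs and is a secondary outcome. The 80% therefore applies to neither coprimary outcome and not to the SMS-plus-education versus education contrast. Nothing elsewhere in the article repairs this.

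The figure is also not supported for EIS: about 31% from the section's own inputs and about 23% in the contrasts as randomised, both two-sided by normal approximation. How far the coprimary outcomes fall short is unknown. The detectable effect runs from about 0.54 SD to 1.28 SD over ICCs of 0.05 to 0.4, unadjusted for baseline and larger with cluster degrees of freedom. Only the 0.4 is the plan's value.

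**What to change.** In the Sample Size Calculation section:

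1. State that the calculation concerns EIS, a secondary outcome, and that no power was calculated for the coprimary outcomes.
2. Correct the 80% figure, or withdraw it if no set of inputs reproduces it.
3. Report the minimum detectable difference for the knowledge, attitude, practice and PPE-use scores in each 4-versus-4 contrast, including SMS plus education versus education alone. Take each score's SD and between-subcounty ICC from the 539 baseline interviews, allow for baseline adjustment, and use cluster degrees of freedom.
4. Reconcile the PPE-use scoring between the two sections before quoting any difference in score points; use SD units until then.
5. Refer to these figures when interpreting non-significant coprimary results.

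The cost is a less favourable stated power and a short calculation on data already held. Enrolment does not change.

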### Statistical Analyses

Statistical analyses will be conducted using Stata (version 15; StataCorp) and R (version 4.3.1; The R Foundation). The outcomes will be based on intention-to-treat analyses, and missing data values will be computed using the multivariate imputation chained equations R package. The effect of the interventions on the 3 arms will be analyzed using the intervention arms as dummy-coded predictors and the follow-up measures as outcomes in multivariate mixed models with the cluster (subcounty) as the random effect. Sensitivity analyses are planned to control for differences in sex, age, educational level, previous training, and annual pesticide use days. For objective 2, subanalyses of factor scores (type of PPE, time taken to change clothing after pesticide handling, postapplication bathing routine, mixing pesticides, and application of pesticides using a knapsack) used to compute the exposure algorithms will be made to test their variation resulting from the interventions.

Intervention effects on KAP, PPE use (frequency of using PPE for all body parts, frequency of using gloves, and exposure modified by pesticide use), algorithm-based pesticide EIS, and health signs and symptoms associated with acute pesticide poisoning will be analyzed in a model testing the control group (0) against the educational intervention (1) and against the educational intervention+RANAS-based SMS text messages (1). For the intervention effects on PPE and glove use (objective 4), all arms will be compared by testing the educational intervention against the educational intervention+RANAS-based SMS text messages (0) in an additional model.

To understand the psychosocial mechanisms of the interventions (objective 5), we will perform 2 mediation models with multiple psychosocial behavioral determinants as mediators, one testing the educational intervention group (1) against the control group (0) and one testing the educational intervention+RANAS-based text message group (1) against the educational intervention (0). The mediation analyses will use the change scores (follow-up value – baseline value) for all RANAS-based psychosocial determinants as mediators and PPE use as the outcome, operationalized as the frequency of using PPE to cover all body parts and using gloves.

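### The only sample size calculation is for EIS with the two intervention arms merged, so it gives no power for the aim 2 contrast, education+SMS versus education on PPE use

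*Protocol article*

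**What the plan says.** The Sample Size Calculation section takes its effect from a survey of trained and untrained farmers: "The trained group had a mean EIS of 0.47 (SD 0.10), and the untrained group had a mean EIS of 0.55 (SD 0.18"). It then states "We assumed that the 2 planned intervention arms would show a similar effect distribution" and on that basis uses a two-sample means test with "a total of 12 clusters equally distributed between the control and intervention groups, and an intraclass correlation coefficient of 0.4". This "resulted in a cluster size of 40 farmers and a total of 480 farmers", for 80% power at the 5% level. Five farmers per cluster are added for dropout, which gives 540. No other calculation is reported.

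Elsewhere the article sets out a different structure:

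- Randomization and Blinding assigns 4 clusters to each of three arms.
- Outcome Measures makes KAP scores and PPE use coprimary and lists EIS as secondary.
- Aims and Specific Objectives gives two main aims. Under the second, the question is whether the SMS messages "have an additional, increased effect on PPE use compared to the educational intervention alone".
- Statistical Analyses plans that test for PPE and glove use: "all arms will be compared by testing the educational intervention against the educational intervention+RANAS-based SMS text messages (0) in an additional model".

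**The concern.** One of the two main aims is a comparison between the two intervention arms. The sample size is obtained by treating those arms as alike and merging them, so it contains no assumed SMS increment, no SD or ICC for PPE use, and no power for the comparison. The contrast also has fewer clusters (8 of the 12) than the calculation uses.

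This affects how a result can be read. The Discussion expects the findings to help identify the most efficient intervention approach and to allow first recommendations on whether targeting psychosocial determinants raises PPE use more than education. If the SMS contrast is not significant and the reader has only the 80% figure in mind, absence of evidence may be taken as evidence that SMS adds nothing.

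**Working it through.** **Inputs.** From Sample Size Calculation: means 0.47 and 0.55, SDs 0.10 and 0.18, ICC 0.4, 40 farmers per cluster, 12 clusters split equally (read as 6 versus 6), 5% level. From Randomization and Blinding: 4 clusters per arm. Two-sided testing is my assumption, as the section does not state it.

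**Step 1: the plan's own figure.** Design effect = 1 + (40 − 1) × 0.4 = 16.6. Each group has 6 × 40 = 240 farmers, an effective 240/16.6 = 14.5.

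- SE of the difference = √[(0.18² + 0.10²) × 16.6/240] = 0.0542.
- 0.08/0.0542 = 1.48, which gives power of about 31% (27% with t on 10 df; 43% if one-sided), not 80%.
- Larger clusters do not help: with unlimited cluster size, power stays at about 32–33%.
- With the pooled split that the randomisation implies, 4 control versus 8 intervention clusters, power is about 25% (separate SDs) or 29% (pooled SD).
- An ICC of about 0.093 would give 80% at 6 versus 6.

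**Step 2: the aim 2 contrast.** The article gives no SD, ICC or increment for PPE use, so I work in SD units and vary both the ICC and the increment. The planning effect supplies a scale: pooled SD = √[(0.10² + 0.18²)/2] = 0.1456, and 0.08/0.1456 = 0.55 SD. I take SMS increments of half (0.275 SD), three quarters (0.41 SD) and all (0.55 SD) of it.

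Variance of a cluster mean = ICC + (1 − ICC)/40. SE of the difference for 4 versus 4 clusters = √(2 × variance/4). At ICC 0.4 the variance is 0.415 and the SE is 0.456 SD.

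Power of the two-sided 5% z-test:

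| ICC | 0.275 SD | 0.41 SD | 0.55 SD |
|---|---|---|---|
| 0.4 | 9% | 15% | 23% |
| 0.05 | 30% | 57% | 82% |
| 0.01 | 55% | 87% | 99% |

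A model with only these two arms has 8 clusters, so t on 6 df is the more realistic reference. It lowers every entry: at 0.55 SD, for example, to about 18% at ICC 0.4 and 67% at ICC 0.05.

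**Step 3: detectable difference.** For 80% power by z-test the difference must be (1.96 + 0.84) × SE. At ICC 0.4 this is 2.80 × 0.456 = 1.28 SD, or about 1.53 SD with t on 6 df.

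**Step 4: if the 80% is accepted.** Suppose the 6-versus-6 figure is right and the ICC is therefore about 0.093. The 4-versus-4 contrast then has about 63% power for an SMS increment as large as the whole planning effect, and about 21% for half of it.

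**The case against.** The section is open about its basis. It names EIS, trained versus untrained farmers, a two-sample test and the similarity assumption, and it nowhere claims 80% power for SMS versus education or for PPE use. That stands: this is a gap in coverage, not a false claim about the contrast.

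Four stronger readings are tempting, and the document does not support them.

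- A reader might infer that the plan assumes aim 2's null hypothesis, so that power equals 5%. The assumption is of similar effects, made for the EIS calculation. Aim 2 concerns PPE use, which is one of five factors in EIS. Power of 5% would follow only if the assumption were carried over to PPE use and read as exact equality.
- A reader might call the SMS contrast coprimary. The article gives that status to the PPE-use outcome and places the contrast in an additional model. The contrast is still the stated test of a main aim.
- A reader might say that no ICC brings power near 80%. That holds for the half-size increment over the ICCs tabulated, but not for the full one, which reaches 82% by z-test at ICC 0.05.
- A reader might say that a non-significant result is the most likely outcome. At ICC 0.01 even the half-size increment has 55% power, so this too depends on the ICC.

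Baseline adjustment, described in the abstract, could raise power by an amount that the document does not allow one to compute. Rules for intervals and interpretation may also sit in an analysis plan that is not shown. Neither point supplies the missing calculation or repairs the 80%.

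**Conclusion.** The concern holds in this limited form: the 80% power behind the 540 farmers does not extend to education+SMS versus education on PPE use, and nothing in the article says what that contrast can detect. At the article's own ICC, power is 9% to 23% over the increments examined, and the detectable difference is about 1.28 SD. Adequate power needs both a much smaller ICC and, at ICC 0.05, an SMS increment about as large as the full planning effect.

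The figures rest on carrying the EIS-based ICC and standardised effect over to PPE use, on clusters of 40, and on no gain from baseline adjustment. That no power is given for aim 2 rests on the text alone. The 80% for the pooled comparison is a further problem, because the stated inputs do not yield it under either the 6-versus-6 or the 4-versus-8 split.

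**What to change.** 1. Restate the Sample Size Calculation section: the calculation concerns EIS, a secondary outcome, for intervention versus control only, and the trial was not sized for education+SMS versus education.
2. Do not leave 80% standing for the pooled comparison. Recompute it for the actual 4:4:4 allocation, or correct the ICC if 0.4 is an error.
3. Give the smallest SMS-versus-education difference in PPE use detectable with 4 versus 4 clusters, using the SD and ICC from the baseline data already collected and a small-sample reference such as t on 6 df.
4. Report the contrast as an estimate with its 95% CI, and do not read non-significance as no added benefit.

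The cost is some wording and a short calculation from existing data. Follow-up is complete, so no farmers or clusters are added and the planned models do not change. The downside is a less favourable power statement, for aim 2 and probably for the pooled comparison as well.
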